
### Who will take informed consent? {26a}

Patients’ written consent will be obtained by the investigator, their oncologist, prior to any study-specific procedures. Participation is voluntary, individuals may withdraw at any stage and participation does not affect the individual’s treatment.

### Additional consent provisions for collection and use of participant data and biological specimens {26b}

Not applicable as no biological specimens were collected as part of this trial.

## Interventions

### Explanation for the choice of comparators {6b}

Peripheral neuropathy refers to symptoms arising from damage to the peripheral nerves. These nerves carry sensation, control arm and leg movements, and control the bladder and bowel. Due to the neuropathy, the patient should avoid injury by paying attention to home safety, such as by using handrails on stairs to prevent falls and potholders in the kitchen to avoid burns. The physician can prescribe over-the-counter pain medications, lidocaine patches, menthol creams, etc. Physical therapy, occupational therapy, and rehabilitation may be helpful to regain function. In some cases, nerve damage may be permanent. The only way to reduce neurotoxicity is to decrease the dose and/or duration of oxaliplatin, which is not feasible when a long, intense dose is needed, especially when the patient has metastatic cancer. If our hypothesis is validated, it will allow us to add this dietary supplement to the patient’s follow-up to reduce neurotoxicity while continuing the chemotherapy.

Spirulina is considered a controlled foodstuff in the European Union. The species *A. maxima* and *A. platensis* are listed under the genus Spirulina (European Parliament and Council Regulation (EC) No 396/2005 of 23 February 2005 on maximum residue levels of pesticides in or on food and feed of plant and animal origin). Spirulina has been the subject of preclinical and clinical studies. Preclinical data showed no toxicity of spirulina at high doses (for administered doses up to 30 g/kg/day or ad libitum in mice). In the numerous clinical studies carried out at doses of up to 19 g/day of dry spirulina, only a few gastrointestinal and headache-type adverse effects relating to the consumption of spirulina were reported. Products containing spirulina may be contaminated with cyanotoxins, bacteria, or trace metal elements (Report of the French Agency for Food, Environmental and Occupational Health Safety (ANSES) available from: https://www.anses.fr/fr/system/files/NUT2014SA0096.pdf). For the placebo, other than rare hypersensitivity reactions to the colorant, there would be no risk given that it is currently used in food.

The quality control information for the drugs being tested, i.e. a dietary supplement and the placebo, will be provided by AlgoSource, which has an ISO 9001:2015-certified Quality Management System.

In relation to the primary objective, the efficacy of the SLPC will be measured at 4 months after the beginning of chemotherapy treatment, corresponding to the ninth cycle of chemotherapy. As mentioned previously, chronic toxicity does not become apparent until cycles 8–10 in the commonly used FOLFOX dosing regimen. The study diagram is shown in Fig. 1.

**Fig. 1 Fig1:**
[figure not shown]
Study diagram

### Intervention description {11a}

Being double blind, the study treatment, the comparator and its corresponding placebo will be managed by the sponsor and AlgoSource. The patient must begin the study treatment 3 days before the chemotherapy regimen. This regimen is counted in cycles that last around 14 days and begin on Day1 (D1) of each chemotherapy cycle. No study treatment must be taken on chemotherapy treatment days.

The SPLC/placebo prescription will cover 1 month of treatment. Participants will be given a patient diary for the entirety of the study. From D3 to D1 before the first chemotherapy cycle: patients will take SPLC or placebo (one ampoule per day, neat or diluted in a glass of water). If vomiting occurs immediately after taking the SLPC dose, the patient should retake the SLPC dose. On chemotherapy days (D1 to D3), the patient does not take SLPC/placebo. From D4 to D14 SLPC/placebo must be taken once a day and 1 h before or 2 h after food and taking the antiemetic. The same schedule will be used during induction chemotherapy for 12 cycles, as shown in Fig. 2A.

**Fig. 2 Fig2:**
[figure not shown]
Schedule of trial treatment in chemotherapy cycles

After induction chemotherapy, the patients on maintenance therapy or targeted therapy will continue to take spirulina for six cycles (3 months) after the last cycle of oxaliplatin (Fig. 2B). The same schedule will be applied for the patients who are not on maintenance chemotherapy (Fig. 2C). The complete trial schedule is shown in Table 2.

**Table 2 Tab2:** Study schedule

Assessments	Inclusion visit D-30 to D-4	Cycle 1	Cycle 1 to 12		Cycle 13 to 18	End of study visit / 28 days after last day of PHYCOCARE® /PLACEBO
		D-3 to D-1	D1 to D3	D4 to D14	D1 to D14	
Informed consent	X					
Medical History	X					
Clinical examination (Performance status (ECOG), vital signs, symptoms)	X		X (D1)		every 28 days	X
ONLS questionnaire	X		at M4 (C9D1)			X
QLQ-C30 questionnaire	X		at M4 (C9D1)			X
EDX	X		at M4 (C9D1)			X
Randomisation	X					
Scanner	at D-42					
PHYCOCARE® or placebo treatment		X		X	X (days without chemotherapy)	
Oxaliplatin-based chemotherapy			X			
Chemotherapy maintenance regimen					If applicable	
Adverse events (AE)		AE assessed at each patient visit				X
Treatment adherence (patient diary)		Compliance assessed at each patient visit				X

Note that the oxaliplatin dose is 85 mg/m^2^ and the dose adjustment is shown in Table 3.

**Table 3 Tab3:** Oxaliplatin dose adjustement

Scale	NCI-CTC grading for neuropathy
Grade 1	Asymptomatic, loss of deep tendon, reflexes, or paresthesia (including tingling), but not interfering with function
Grade 2	Sensory alteration or paresthesia (including tingling) interfering with function, but not ADL
Grade 3	Sensory alteration or paresthesia interfering with ADL
Grade 4	Disabling

### Criteria for discontinuing or modifying allocated interventions {11b}

The study treatment can be discontinued early at any time: at the request of the patient, whatever the reason; at the request of the investigator for any reason in keeping with the patient’s best interests; at the request of the sponsor; in case of non-confirmation of the selection criteria; and in case of unacceptable toxicity.

### Strategies to improve adherence to interventions {11c}

Patient adherence to treatment will be assessed at each visit and at the end of the study through the patient diary.

### Relevant concomitant care permitted or prohibited during the trial {11d}

Any drug deemed necessary for the patient’s well-being may be administered by the investigator. However, patients are not permitted to take plant-based therapy (gemmotherapy or phytotherapy).

### Provisions for post-trial care {30}

At the end of the clinical research, the patient will be followed up by their oncologist and will benefit from the usual care for their disease.

The sponsor has taken out an insurance policy covering the financial consequences of its civil liability in compliance with the regulations.

### Outcomes {12}

The primary endpoint is the rate of neurotoxicity according to US NCI (National Cancer Institute) criteria in both arms 4 months after the beginning of oxaliplatin-based regimen. NCI criteria are listed in Table 4.

**Table 4 Tab4:** US National Cancer Institute common toxicity criteria (NCI-CTC)

Oxaliplatine dosage adjustment according to neurotoxicity				
Neurotoxicities	Grade	Toxicity duration		
		1 to 7 days	> 7 days	Persistent between cycles^**a**^
Paresthesias/dysesthesias^b^ that do not interfere with fine motor skills	1	No dose reduction		
Paresthesias/dysesthesias^b^ that interfere with fine motor skills but do not affect activities of daily living (ADLs)	2	No dose reduction		75% of the dose
Paresthesias/dysesthesias^b^ with pain or decreased fine motor skills that affect activities of daily living (ADLs)	3	1st time: 75% of the dose 2nd time: 50% of the dose		Discontinue treatment
Persistent or incapacitating or lifethreatening paresthesia/dysesthesia	4	Discontinue treatment		
Acute toxicity: laryngeal-pharyngeal dysesthesia^b^ (during or within 2 h after infusion)	NA	Extend the oxaliplatin infusion to 6 h on the next treatment.	NA	

^a^Toxicity still present at the beginning of the next cycle

^b^May be caused by the cold

The secondary outcomes are:⇨ Time frame for definitive discontinuation or decrease in oxaliplatin treatment. The dose or discontinuation of oxaliplatin will be noted at each chemotherapy visit, in accordance with the process established in Table 3⇨ Dose intensity of oxaliplatin noted at each chemotherapy visit (see Table 3)⇨ Neurological adverse events at the following hospital visits: baseline, M4, and M9/termination visit⇨ Nerve electrodiagnostic examination (EDX) and neurology questionnaire: Overall Neuropathy Limitation Scale (ONLS) French translation according to Graham et Hugues [14] at baseline, M4 and M9/termination visit⇨ Adverse Events collected at each chemotherapy visit or in patient diary⇨ Quality of life questionnaire: QLQ C30 at baseline, M4 and M9/termination visit

Note that when a patient discontinues the study treatment early for whatever reason, an early termination visit will be conducted if the patient’s condition allows.

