### Sample size {14}

Simon’s two-stage design [15] will be used. The null hypothesis that the true response rate is 0.60, the proportion of neurotoxicity targeted, will be tested against a one-sided alternative. In the first stage, 31 patients will be accrued. If there are 18 patients or fewer with grade 1 neurotoxicity among these 31 patients in the SLPC arm, the study will be halted. Otherwise, 24 additional patients will be accrued, making a total of 55. The null hypothesis will be rejected if 38 or more responses are observed in 55 of the SLPC arm patients. With a type I error rate of 0.05 and a power of 0.90, 55 patients will be enrolled in each arm, that is to say, 110 patients.

All the previous hypotheses account for a lost-to-follow-up rate at 4 months of 20%.

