### Plan to promote participant retention and complete follow-up {18b}

The target population of the trial is cancer patients during chemotherapy treatment; missing data could only result from withdrawal of consent or a serious adverse event (SAE). There is no plan for promoting participant retention.

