## Statistical methods

### Statistical methods for primary and secondary outcomes {20a}

Descriptive analyses will be conducted for all variables collected. Point estimates and 95% confidence intervals will be calculated for qualitative and quantitative variables. For estimates obtained using a small sample, the medians and interquartile intervals (for quantitative variables) and exact confidence interval (for qualitative variables) will be provided. All analyses will be performed with the use of R software (version 4.0) or SAS software (version 9.4).

To fulfill the main objective of this study, the prevalence of neurotoxicity of grade 2 or above in both arms will be estimated using linear mixed regression, taking into account the center effect (random effect). The second step will be to adjust this estimate based on known risk factors (gender, age, etc.).

For the secondary analyses:Comparison of time before cessation or reduction of chemotherapy treatment will be estimated using the Kaplan-Meier method and tested with the log-rank test;Comparison of patients with a decrease in treatment due to neurological toxicity will take place via mixed linear regression on both treatment arms;Progression of grades 3 and 4 neurological adverse events at baseline, M4, and M9 (or at the last visit if earlier) will be tested using mixed linear regression with a random center effect;EDX data will be compared using Fisher’s exact test and the Wilcoxon-Mann-Whitney test;The chi-square test or Fisher’s exact test will be used to compare Adverse Events in both arms;Progression of grades 3 and 4 neurological QLQ C30 at baseline, M4, and M9 (or at the last visit if earlier) will be tested via mixed linear regression with a random center effect; andMedian progression-free survival will be estimated and plotted using the Kaplan-Meier method and the response rate will be estimated as a percentage with a 95% confidence interval.

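### The exit visit is tied to stopping the supplement, and nothing secures the month-4 primary assessment for patients who stop before cycle 9

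*Protocol article*

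**What the plan says.** **Primary time point.** Outcomes {12} sets the primary endpoint as the NCI neurotoxicity rate "in both arms 4 months after the beginning of oxaliplatin-based regimen". Table 2 places the month-4 ONLS, QLQ-C30 and EDX at C9D1.

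**Exit.** The same section says that "when a patient discontinues the study treatment early for whatever reason, an early termination visit will be conducted", if the patient's condition allows. The late time point is written jointly with termination: "Neurological adverse events at the following hospital visits: baseline, M4, and M9/termination visit". The last column of Table 2 reads "End of study visit / 28 days after last day of PHYCOCARE® /PLACEBO". Section {11b} lets the study treatment stop at the wish of the patient, the investigator or the sponsor, when selection criteria are not confirmed, and "in case of unacceptable toxicity". It does not mention follow-up after a stop.

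**Missing data.** The retention section {18b} says that "missing data could only result from withdrawal of consent or a serious adverse event (SAE") and that there is no retention plan. Sample size {14} allows for "a lost-to-follow-up rate at 4 months of 20" percent. Section {20c} plans estimates in a modified intention-to-treat population, with multiple imputation of the grade as a sensitivity analysis for the primary objective.

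**Month 9.** Section {20a} analyses grade 3–4 neurological events and QLQ-C30 at baseline, M4 and M9, "or at the last visit if earlier".

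**The concern.** The primary endpoint belongs to a fixed time after the start of oxaliplatin, but the patient's last visit is tied to the last dose of supplement or placebo. A patient who stops the supplement before cycle 9 for intolerance or by choice, without withdrawing consent, may still come to the same department about every 14 days for oxaliplatin. A site that follows the text would nevertheless hold a termination visit and could reasonably close the patient out. The month-4 grade would then be lost although it could have been observed.

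If the reasons for stopping are related to neurotoxicity, the rate among those remaining is not the rate among all randomised patients. Separately, if an early last visit stands in for month 9, the secondary analyses mix patients seen at very different oxaliplatin exposures.

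**Working it through.** **1. Does the text point to exit?** Four statements set side by side:
- The visit is called a termination visit and is triggered by stopping the study treatment ({12}).
- Table 2 names the visit after the last dose the end of study.
- The 11-month participation period ({13}) fits up to 30 days of screening, 9 months of treatment and 28 days.
- Section {20a} expects some patients to have a last visit before M9.

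No statement keeps C9D1 for a patient who has stopped. Exit is therefore the natural reading, though not an express rule.

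**2. Which stops matter?** Inputs: 14-day cycles ({11a}) and the 28-day interval in Table 2.
- C9D1 = 8 × 14 + 1 = day 113.
- Stop at the end of cycle 4: day 56; final visit 56 + 28 = day 84, before day 113.
- Stop at the end of cycle 6: day 84; final visit day 112, still before day 113.
- Stop at the end of cycle 7: day 98; final visit day 126, after day 113.

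The article gives no timing for the early termination visit. With the 28-day interval, stops up to about the end of cycle 6 lose C9D1. If the visit is held at once, any stop before cycle 9 does.

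**3. The plan's own figures.** 20% of 55 = 11 patients per arm without a month-4 grade. The share due to stopping the supplement is not given. The stated two-stage rule (continue if more than 18 of 31, reject if at least 38 of 55) does not reproduce its stated error rates: exact calculation gives a type I error of 0.104 at 0.60. Power is 0.980 at an assumed 0.80, that is, grade 2 or above halved from 40% to 20%. That is a separate matter and is noted only because the rule is used in step 5.

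**4. Illustrative bias if stoppers are left out.** Take response as no grade 2 or above, with a true rate of 0.60. Let d be the share missing and q their response rate. Observed rate = (0.60 − d·q)/(1 − d).

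| d | q = 0 | q = 0.4 | q = 0.6 |
|---|---|---|---|
| 5% | 0.632 | 0.611 | 0.60 |
| 10% | 0.667 | 0.622 | 0.60 |
| 20% | 0.750 | 0.650 | 0.60 |

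There is no bias when the missing patients respond like the rest (q = 0.6).

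**5. Illustrative cost if missing counts as non-response.** The response probability becomes 0.80 × (1 − d). Power of the stated rule falls from 0.98 to 0.91 (5%), 0.73 (10%) and 0.26 (20%).

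**6. Exposure when an early visit stands for M9.** The oxaliplatin dose is given as 85 mg/m². By day 84 six infusions have been given (the seventh is due on day 85): at most 6 × 85 = 510 mg/m². Twelve cycles without reduction give 12 × 85 = 1,020 mg/m². Section {6b} says chronic toxicity does not show until cycles 8–10, and the Discussion says symptoms become more likely beyond 780–850 mg/m². A day-84 visit precedes both.

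**The case against.** A reader might infer that the termination visit replaces C9D1, so that the endpoint is missing by design in exactly the patients whose stopping depends on outcome. The document does not support that.

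- No section cancels C9D1. The termination visit is paired with M9, M4 is listed separately, and Table 2 does not make C9D1 conditional on taking the supplement.
- Stopping oxaliplatin for neuropathy does not itself trigger termination, because the supplement runs on for six more cycles after oxaliplatin ends. Toxicity is one listed reason for stopping among several.
- The primary endpoint is a clinical grade. Adverse events are collected at each visit, and the dose-adjustment rules (printed under the Table 4 caption) need a neurotoxicity grade at each oxaliplatin cycle. A patient still on oxaliplatin may well have a grade in the hospital record.
- The closed list in {18b} could itself mean that stopping the supplement does not end follow-up.
- The 20% may be largely deaths, progression or withdrawn consent, which no change here would recover. A worst-case range such as 30/55 to 41/55 (55% to 75%), from an invented 30 responders among 44 observed, would apply to any 20% loss and does not measure this one.
- The allowance for loss and the imputation are already planned, and an article may leave follow-up detail to the full protocol.

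These points limit the claim but do not remove it. Study collection of adverse events is scheduled only up to the end-of-study visit. The 20% allowance covers numbers, not selection. Imputation is a sensitivity analysis and a poor substitute for a grade that could be observed. Nor is this mere silence: the article states an exit trigger, a closed list of causes of missing data and a last-visit rule, and taken together they do not fit.

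**Conclusion.** The point holds in limited form. The termination or end-of-study visit is tied to stopping the supplement for any reason, and nothing secures the C9D1 grade when the stop comes before cycle 9. On the natural reading those patients leave without the primary endpoint. This is an inference from the exit wording, not an express rule.

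The loss may be related to outcome; the document does not show that it is. Its size is not stated: it is some part of the assumed 11 of 55 per arm. The bias and power figures are illustrations that rest on assumed d, q and a response rate of 0.80 under the alternative.

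Two further statements need correction whatever that size. The list of causes of missing data in {18b} leaves this route out and sits badly with the 20% in {14}. The last-visit wording in {20a} treats early, low-exposure visits as M9; it affects secondary analyses only.

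An amendment is worthwhile while patients are on study, since a grade that nobody records at month 4 is hard to recover later. The flaw does not invalidate the design.

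**What to change.** - In {11b} and {12}, state that stopping SLPC or placebo is not leaving the study.
- Unless consent is withdrawn, collect the NCI neurotoxicity grade, with the ONLS, QLQ-C30 and EDX already planned, at month 4 and month 9 whatever the supplement status. Fix a calendar day for month 4 (day 113 by the schedule) for patients no longer on chemotherapy.
- Include these patients in their randomised arm.
- In {20a}, analyse data from an early termination visit at its actual time and not as M9.
- Reconcile {18b} with {11b}, {12}, {14} and the last column of Table 2.

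The cost is a protocol amendment. The assessments are already scheduled for every patient, and those still on chemotherapy attend anyway. The downside is a few extra visits for patients no longer on chemotherapy.

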### Participant timeline {13}

The participants’ treatment period corresponds to 9 months (18 cycles) and the participation period to 11 months.

### Sample size {14}

Simon’s two-stage design [15] will be used. The null hypothesis that the true response rate is 0.60, the proportion of neurotoxicity targeted, will be tested against a one-sided alternative. In the first stage, 31 patients will be accrued. If there are 18 patients or fewer with grade 1 neurotoxicity among these 31 patients in the SLPC arm, the study will be halted. Otherwise, 24 additional patients will be accrued, making a total of 55. The null hypothesis will be rejected if 38 or more responses are observed in 55 of the SLPC arm patients. With a type I error rate of 0.05 and a power of 0.90, 55 patients will be enrolled in each arm, that is to say, 110 patients.

All the previous hypotheses account for a lost-to-follow-up rate at 4 months of 20%.

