### Interim analyses {21b}

A futility analysis will be performed according to Simon’s method [15]. Enrolment will continue during the futility analysis. The study will be halted if there are fewer than 18 responders (i.e., patients with grade 1 neurotoxicity) in the first 31 patients enrolled in the SLPC arm.

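### The 38-of-55 success rule has an exact type I error of 0.104 when all 55 SLPC patients are evaluable, not the stated 0.05; at the plan's own 20% loss the same cut-off leaves almost no power

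*Protocol article*

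**What the plan says.** All of the design is in the protocol article, Sample size {14}: "Simon’s two-stage design [15] will be used". The null is fixed there: "The null hypothesis that the true response rate is 0.60, the proportion of neurotoxicity targeted, will be tested against a one-sided alternative". Stage 1: "In the first stage, 31 patients will be accrued", with the futility rule "If there are 18 patients or fewer with grade 1 neurotoxicity among these 31 patients in the SLPC arm, the study will be halted". Stage 2: "Otherwise, 24 additional patients will be accrued, making a total of 55". The success rule is "The null hypothesis will be rejected if 38 or more responses are observed in 55 of the SLPC arm patients", and the claimed operating characteristics are "With a type I error rate of 0.05 and a power of 0.90, 55 patients will be enrolled in each arm". The section closes by saying that its assumptions allow for 20% loss to follow-up at 4 months.

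Interim analyses {21b} words the stage 1 bound differently: "The study will be halted if there are fewer than 18 responders (i.e., patients with grade 1 neurotoxicity) in the first 31 patients enrolled". That stops at 17 or fewer rather than 18 or fewer.

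No alternative response rate is given. Objectives {7} speaks only of a 50% decrease in neurotoxicity of grade 2 or above at cycle 9.

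**The concern.** The null rate, both stage sizes and both boundaries are printed, so the type I error can be computed exactly without a value for the alternative. Under the null, 55 patients yield 33 responses on average, so a cut-off of 38 is only five above expectation. That looks lenient for a 5% test.

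Trial design {8} calls the study non-comparative and not powered to compare the arms. The count of 38 in 55 is therefore the only efficacy threshold in the plan (the 18-of-31 bound is a futility threshold). If its error rate is misstated, the reader cannot tell how strong a positive result would be. The 20% loss adds a second question: whether 38 is meant to apply to 55 patients enrolled or to a smaller number with a month-4 assessment.

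**Working it through.** **Inputs.** From Sample size {14}: p0 = 0.60, one-sided; n1 = 31, stop at ≤18; n2 = 24, N = 55; reject at ≥38; stated type I error 0.05 and power 0.90; loss 20%. From Interim analyses {21b}: stop at ≤17. Assumption: p1 = 0.80, taking 1 − 0.60 = 40% as the null rate of grade ≥2 and halving it to 20%. The type I error does not use p1.

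**Formula.** P(reject | p) = Σ over x = 19..31 of b(x; 31, p) × P(Bin(24, p) ≥ 38 − x).

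**1. The stated 0.05, at p = 0.60**

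| x | b(x; 31, 0.60) | P(Bin(24, 0.60) ≥ 38 − x) | product |
|---|---|---|---|
| 19 | 0.1443 | 0.0400 | 0.0058 |
| 20 | 0.1298 | 0.0960 | 0.0125 |
| 21 | 0.1020 | 0.1919 | 0.0196 |
| 22 | 0.0696 | 0.3279 | 0.0228 |
| 23 | 0.0408 | 0.4891 | 0.0200 |
| 24 | 0.0204 | 0.6502 | 0.0133 |
| 25 | 0.0086 | 0.7870 | 0.0068 |
| 26–31 | | | 0.0036 |

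The unrounded sum is **0.1042**, and 0.1042 / 0.05 = 2.08. The stated figure is not reproduced.

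**2. Other readings of the rule**

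- Stop at ≤17 (Interim analyses {21b}): 0.1061.
- No futility stop, P(Bin(55, 0.60) ≥ 38): 0.1066.
- Cut-off read as more than 38: 0.0625.
- 0.60 read as the neurotoxicity rate, so a null response rate of 0.40: about 0.00001, with power 0.615 at 0.70.

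None gives 0.05. It is not a matter of discreteness either. With N = 55 the attainable levels are 0.1042 (≥38), 0.0625 (≥39) and 0.0345 (≥40), so 38 lies two steps below the first cut-off that meets 0.05.

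**3. Power of the printed rule with 55 evaluable.** It is 0.615 at p1 = 0.70, 0.872 at 0.75 and 0.980 at 0.80. It reaches 0.90 at p1 of about 0.758.

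**4. Fewer evaluable patients, cut-off held at 38.** Same formula, with stage 1 kept at 31 and the shortfall taken from stage 2. At 20% loss, 55 × 0.80 = 44.

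| evaluable | type I error | power at 0.80 |
|---|---|---|
| 55 | 0.104 | 0.980 |
| 54 | 0.076 | 0.968 |
| 53 | 0.053 | 0.948 |
| 52 | 0.035 | 0.918 |
| 50 | 0.013 | 0.814 |
| 44 | 0.0001 | 0.20 |

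At 44, the cut-off asks for 38/44 = 86% responders, above the assumed alternative of 80%. If the lost 20% count as non-responders among 55, the null rate becomes 0.60 × 0.80 = 0.48 and the alternative 0.80 × 0.80 = 0.64: type I error 0.0012, power 0.26.

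**5. Boundaries that meet 0.05 and 0.90 at p1 = 0.80**

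- ≤18/31, then ≥40/55: type I error 0.0345, power 0.930.
- ≤15/26, then ≥33/45: type I error 0.0445, power 0.9001.
- ≥40 with only 44 evaluable: power about 0.04.

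**The case against.** The strongest reply is that 0.104 describes a situation the plan does not expect. The section allows for 20% loss, so about 44 SLPC patients should be evaluable, and there a cut-off of 38 is far too strict rather than too lenient. This stands as a limit on the consequence. A reader might infer that an inactive supplement will be declared promising about one time in ten; that is true only if all 55 are evaluable (or the section's loss allowance does not apply to this count). It does not rescue the stated figures, because the power then falls to about 0.20.

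The rule does meet both targets in between: with 52 evaluable it gives 0.035 and 0.918 at 0.80. But that is a loss of about 5%, and the document gives neither 52 patients nor that loss rate; with 53 evaluable the level is already above 0.05.

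A second reply is that the power claim cannot be called wrong when no alternative is printed. This also stands. A reader might conclude that the 0.90 is false, but the rule has 0.90 power at an alternative of about 0.758, and 0.80 is inferred from the halving in Objectives {7}. Only the 0.05 is contradicted outright.

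Finally, this is a phase 2-style screening trial, for which a level of 0.10 may be acceptable. That is a modest mitigation, since the plan commits itself to 0.05.

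**Conclusion.** The type I error stated in Sample size {14} is wrong for the rule printed beside it: 0.104 with 55 evaluable patients, or 0.106 with the other stopping bound, against 0.05. This rests only on printed inputs and the exact binomial distribution. The power figures rest in addition on an assumed alternative of 0.80. At the plan's own 20% loss, with the cut-off held fixed, the error runs the other way: type I error about 0.0001 and power about 0.20. So 0.05 and 0.90 do not hold together at 55 evaluable (the level fails) or at 44 (the power fails, under 0.80).

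A reader might also try to infer how 38 was arrived at, for instance by inflating the boundaries of a smaller design for drop-out. The document does not say, and the finding does not need it.

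**What to change.** Before outcome data are reviewed, state the alternative response rate (0.80 if a fall from 40% to 20% is meant), say whether the boundaries count evaluable or enrolled patients, and use one stage 1 bound in both sections. Then take one of these routes:

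- **55 evaluable SLPC patients analysed:** reject at 40 or more of 55 (type I error 0.035, power 0.93 at 0.80).
- **About 44 to 45 evaluable expected:** use exact boundaries for that number, for example stop at 15 or fewer of 26 and reject at 33 or more of 45 (0.044 and 0.900), and provide for recomputing the cut-off at the number actually evaluable.
- **38 of 55 kept:** restate the type I error as 0.104.

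The cut-off should not be changed from 38 to 40 on its own: with 44 evaluable, power at 0.80 would drop from about 0.20 to about 0.04.

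The first and third routes change a figure in the text and need no extra enrolment if 55 are in fact evaluable. The second replaces the set of boundaries. Its power at 45 is only just 0.90, and expecting 45 evaluable at 20% loss needs 45 / 0.80 = 56.25, that is 57 enrolled per arm rather than 55. Otherwise a small loss of power has to be accepted and stated.

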### Objectives {7}

The primary objective is to demonstrate a 50% decrease in neurotoxicity grades of 2 or above at cycle 9 (4 months after the start of oxaliplatin-based chemotherapy) in the SLPC arm.

The secondary objectives are to compare the following in both arms:➢ Percentage of patients who stopped oxaliplatin due to neurological toxicity➢ Percentage of patients with an oxaliplatin dose decrease➢ Neurological toxicities according to the Common Terminology Criteria for Adverse Events (CTCAE) v5.0➢ Overall toxicity (including hematological toxicity, gastrointestinal toxicity, etc.)➢ Patient’s quality of life according to the EORTC-QLQ-C30 questionnaire

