## Assignment of interventions: allocation

### Sequence generation {16a}

Randomization will be conducted blindly by center, neuropathy (stage 0 or 1), and age (< 65 years old and ≥ 65 years old). Wrongly enrolled randomized patients will not be replaced. It will be block balanced in a 1:1 ratio. The software used for the randomization is SAS version 9.4.

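### The Simon cut-offs (18/31, then 38/55) are set on the number enrolled, so they contain no allowance for the claimed 20% loss and do not deliver alpha 0.05 with power 0.90

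*Protocol article*

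**What the plan says.** The Sample size section says "Simon’s two-stage design [15] will be used" and sets the null: "The null hypothesis that the true response rate is 0.60, the proportion of neurotoxicity targeted, will be tested against a one-sided alternative". Stage 1 takes 31 SLPC patients and stops the study at 18 or fewer responders. "Otherwise, 24 additional patients will be accrued, making a total of 55". The null is rejected at 38 or more responses in the 55 SLPC patients. Alpha is given as 0.05, power as 0.90 and enrolment as 55 per arm, 110 in all. The section closes with "All the previous hypotheses account for a lost-to-follow-up rate at 4 months of 20" per cent.

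No alternative response rate is printed. The Objectives section aims to "demonstrate a 50% decrease in neurotoxicity grades of 2 or above at cycle 9". The section on non-adherence and missing data names a modified intention-to-treat population for the prevalence estimates, and multiple imputation as a sensitivity analysis for the primary objective. Neither says how a patient without a month-4 grade enters the 18/31 or 38/55 count.

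**The concern.** An allowance for loss normally shows up as a gap between the number enrolled and the number the decision rule counts. Here both are 55. If one patient in five has no grade at month 4, about 44 SLPC patients remain, and 38 responses would mean 38/44 = 86%, above the 80% that the objective appears to aim for.

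This is the trial's only formal decision rule, and it governs both the futility stop and the primary conclusion. If the cut-offs stay fixed under 20% loss, an effective product would probably be judged a failure. If they are adapted once the evaluable number is known, the error rates depend on a choice the protocol does not make.

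**Working it through.** **Inputs.** From the Sample size section: null rate p0 = 0.60; stage 1 n1 = 31, stop at ≤18; total n = 55, reject at ≥38; alpha 0.05; power 0.90; loss 20%. Alternative p1: not printed. If 0.60 is the rate of patients without grade 2 or above, the null rate of grade 2 or above is 1 − 0.60 = 0.40. Halving it gives 0.20, so p1 = 1 − 0.20 = 0.80. This is an inference, so I also show 0.75 to 0.90.

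**Formula.** With X1 ~ Bin(31, p) and X2 ~ Bin(24, p):

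P(reject | p) = Σ over x = 19 to 31 of P(X1 = x) × P(X2 ≥ 38 − x).

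**Step 1: the printed rule with complete data.**
- p = 0.60: 0.104 (stated alpha 0.05)
- p = 0.75: 0.872
- p = 0.80: 0.980 (stated power 0.90)

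The stated pair is not reproduced. The Interim analyses section words the futility stop as fewer than 18. Using ≤17 instead of ≤18 changes little (0.106 and 0.982).

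**Step 2: 20% loss, cut-offs fixed, lost patients counted as non-responders.** The response probability per enrolled patient becomes 0.8p.
- Null: 0.8 × 0.60 = 0.48, alpha 0.001
- p1 = 0.80: 0.8 × 0.80 = 0.64, power 0.257; probability of stopping at stage 1 is 0.304
- p1 = 0.75: power 0.104
- p1 = 0.85: power 0.488
- p1 = 0.90: power 0.733

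By amount of loss at p1 = 0.80:

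| Loss | Power | Alpha |
|---|---|---|
| 0% | 0.980 | 0.104 |
| 5% | 0.905 | 0.044 |
| 10% | 0.733 | 0.016 |
| 15% | 0.488 | 0.005 |
| 20% | 0.257 | 0.001 |

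**Step 3: exactly 44 evaluable (55 × 0.8), cut-off still 38.** P(Bin(44, 0.80) ≥ 38) = 0.196.

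**Step 4: only evaluable patients count, cut-offs scaled.** Stage 1: 31 × 0.8 = 24.8, about 25, and 18/31 × 25 = 14.5, so stop at ≤14. Final: 38/55 × 44 = 30.4, so 31 is the nearest whole cut-off that keeps the proportion.

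| Reject at | Alpha | Power at 0.80 |
|---|---|---|
| ≥31 of 44 | 0.101 | 0.955 |
| ≥32 of 44 | 0.056 | 0.914 |
| ≥33 of 44 | 0.028 | 0.846 |

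None of the three has alpha at or below 0.05 together with power of at least 0.90.

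**Step 5: is 55 per arm too few?** A search over Simon designs for 0.60 against 0.80 at alpha 0.05 and power 0.90 gives a minimax design of ≤15/26, then ≥33/45 (alpha 0.0445, power 0.900). Allowing for 20% loss, 45/0.8 = 56.25, so 57 per arm; 45 × 1.2 = 54. The planned 55 lies between these. The same design times 1.2 is 18.0/31.2 for stage 1, and its final limit of 32 of 45 becomes 38.4/54, close to the printed 18/31 and 38/55. It therefore looks as though the cut-offs were inflated together with the sample size. That is conjecture, and the conclusion does not depend on it.

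**The case against.** The strongest reply is that 0.26 is conditional. It needs p1 = 0.80, which is not printed, and it needs every lost patient to be a non-responder against a fixed 38, which no section prescribes. The modified intention-to-treat wording may point to an analysis of evaluable patients, and the full protocol or SAP may define it. With scaled cut-offs power stays at 0.85 or above. This stands as a reason to report a range. It does not rescue the printed figures, because the article fixes the cut-offs and the alpha/power pair, and no reading examined at 20% loss or with complete data yields that pair.

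A second reply is that a loss of about 5%, counted as non-response, gives roughly the stated values (0.044 and 0.905). True, but the protocol claims 20%.

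Three stronger readings are tempting and are not supported:
- A reader might infer that the trial is too small and needs 55/0.8 = 69 per arm. That holds only if 55 evaluable patients were required. Step 5 shows that 44 to 45 are about enough.
- A reader might infer that patients who stop SLPC or placebo go ungraded at cycle 9, since "when a patient discontinues the study treatment early for whatever reason, an early termination visit will be conducted". The sentence does not say that they leave the trial or miss the month-4 grading, and adverse events are collected at each chemotherapy visit.
- A reader might see a contradiction in the retention section's statement that "missing data could only result from withdrawal of consent or a serious adverse event (SAE". It names causes of missing data and gives no rate, so it is compatible with 20%.

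**Conclusion.** The point holds as a fault in the cut-offs. They are tied to the enrolled number, so the claimed allowance for 20% loss is not in the rule, and the stated operating characteristics are wrong with or without loss. The type I error of 0.104 with complete data rests only on the printed null and cut-offs, so it is the firmest result. The power figures rest on the inferred p1 of 0.80. Under 20% loss with fixed cut-offs, power falls short of 0.90 at every p1 from 0.75 to 0.90. The size of the shortfall depends on p1 and on how lost patients are counted, which the article leaves open.

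**What to change.** Keep 110 randomised. In the Sample size section, state p1, define both stages on SLPC patients with a month-4 (cycle 9 day 1) grade, say how patients without a grade are treated in the rule, and restate the cut-offs with their exact alpha and power. Align the Interim analyses section with the result. Do this before the interim count.

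One option that fits 55 per arm is to stop at ≤17 of 26 evaluable and reject at ≥32 of 44: alpha 0.0498, power 0.891 at p1 = 0.80. Its costs are:
- Stated power becomes 0.89.
- The chance of stopping early at p1 = 0.80 rises from 0.4% under the printed rule to 5.9%.
- The interim needs 26 evaluable patients, and 31 × 0.8 gives only about 25, so the look comes slightly later (26/0.8 = 32.5, about 33 enrolled).
- The final cut-off of 32 is right only at 44. With 42 evaluable, power falls to 0.79; with 46, alpha rises to 0.091. The protocol should therefore fix in advance a rule for recomputing the cut-off at the evaluable number actually reached.

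The alternative is to stop at ≤15 of 26 and reject at ≥33 of 45. It has alpha 0.0445, power 0.900 and only a 0.8% chance of stopping early at p1 = 0.80, but needs about 57 per arm (114 in all). The first option adds no patients; the second adds four.
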